### **12.2 Secondary Variables - Safety**

#### Haemodynamics

- SAP, DAP, MAP, HR, CVP
- CI, SV, SVR using oesophageal Doppler and PiCCO
- cumulative dose of norepinephrine (mcg/h)
- intrathoracic blood volume index (ITBVI) and extravascular lung water index (EVLWI) (PiCCO)

#### Measurements

of SAP, DAP, MAP, HR, CVP

- baseline
- intraoperatively according to dosing algorithm cycle: *i.e. in 15 min intervals when no volume optimisation, or 15 minutes after new optimised stroke volume*
- at the end of surgery

- on ICU every 6 hours
- of CI, SV and SVR (oesophageal Doppler and PiCCO)
- baseline
  - intraoperatively according to dosing algorithm cycle: *i.e. in 15 min intervals when no volume optimisation, or 15 minutes after new optimised stroke volume*
  - at the end of surgery
  - PiCCO only: on admission to ICU, 6 hours after admission, from post-op day +1 every 12 hours (morning and evening)
- of ITBI and EVLWI (PiCCO)
- baseline
  - every 60 minutes after start of surgery
  - end of surgery
  - on ICU at admission and 6 hours thereafter, from 1st post-op day on 12-hourly (morning and evening)

#### Blood gas analysis and acid-base status, electrolytes

- pCO2, pO2, HCO3, SaO2
- pH, base excess, bicarbonate, lactate
- sodium, potassium, ionized calcium, chloride

Blood will be sampled as close as possible to the time, at which the corresponding hemodynamic measurement is performed. Measurements will be at

- baseline: arterial blood sample
- intraoperatively (every 60 minutes), arterial blood sample
- postoperative (at the end of surgery): arterial blood sample
- on ICU (including postoperative day 1) on admission, 6 hours after admission, on POD 1 every 6 hours venous or arterial blood gas sample

#### Postoperative inflammatory reaction

- IL6 (facultative), IL10 (facultative), PCT, CRP
- SIRS-criteria (body temperature, leucocytes, HR, pCO2)

Measurements will be facultative for IL6, IL10

- baseline
- end of surgery
- 1st postoperative day in the morning

PCT, CRP

- baseline
- 1st postoperative day in the morning

SIRS-criteria

- 1st postoperative day in the morning
- on ICU once daily (in the morning)

#### Renal function

- diuresis/urinary output
- Serum: creatinine, BUN (calculated from serum urea measurement), HbA1c
- Urine: creatinine,  $\alpha$ 1-Mikroglobulin ( $\alpha$ 1-MG), N-Acetyl- $\beta$ -D-Glucosaminidase ( $\beta$ -NAG)

Measurements will be

Diuresis

- intraoperatively cumulative every 60 min
- on ICU 24 hours period

BUN,  $\beta$ -NAG,  $\alpha$ 1-MG

- baseline
- 1st postoperative day in the morning
- on ICU once daily in the morning

Creatinine

- baseline
- 1st postoperative day in the morning
- on ICU once daily in the morning
- serum creatinine: postoperative days 3 and 7 in the morning

HbA1c

- baseline

### Haemostasis

- PT, aPTT, Fibrinogen
- vWF-Ag, vWF-Ristocetin-Cofaktor (vWF-RiCo),
- FVIII:c,
- ROTEM derived parameters: CT, CFT, MCF (ExTEM and FibTEM)

Measurements will be

- baseline
- intraoperatively: 1h after start of operation (ROTEM only)
- at the end of surgery
- 1st postoperative day in the morning (PT, aPTT, vWF-Ag, vWF-RiCo, ROTEM)

### Cardiac function

- Troponin or high-sensitivity Troponin
- NT-Pro-BNP

Measurements will be

- baseline
- end of surgery
- 1st postoperative day

### Other

- PONV (postoperative nausea and/or vomiting)
- Adverse events will be documented with start of administration of Investigational product throughout surgery and postoperatively on ICU until postoperative day 5 (including). Serious adverse events that are not yet resolved at the POD 5 will be followed up until study end.

Circulating blood volume (mLs): Calculation will use the following formulas:

- males:  $((0.3669 \times \text{height (m)} + 0.03219 \times \text{weight (kg)} + 0.6041) \times 1000$
- females:  $((0.3061 \times \text{height (m)} + 0.03308 \times \text{weight (kg)} + 0.1833) \times 1000$   
(Nadler S, Surgery 1962, Mercuriali F, Curr Med Res Opin 1996).
- baseline
- 1st postoperative day (if weight measurement can be performed)

Requirements of blood products (EC, FFP, PC, plasma derived coagulation factor concentrates) and intraoperative blood loss (suction volume)

NOTE: measurements on ICU (if not otherwise mentioned) will be performed until “fit for discharge criteria are fulfilled or until day +5 (incl. day +5) whatever occurs first. Adverse events and adverse reactions will be recorded until post-op day +5. At three months after surgery the patient will be interviewed for health related quality of life (HRQoL).

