|  | 
postoperative day every 6 hours, on ICU* from post-op day +2 until post-op day +5 once daily
 
 
▪ Cardiac function: Troponin or high-sensitivity Troponin, NT-Pro-BNP – measurements: baseline, end of surgery, 1st postoperative day morning
 
▪ inflammatory reaction 
 
○ facultative: IL6, IL 10, IL6/IL10-ratio – measurements: baseline, end of surgery, 1st postoperative day in the morning
 
○ PCT, CRP baseline, 1st postoperative day in the morning
 
○ SIRS-criteria (body temperature, leucocytes (WBC), HR, pCO2), 1st postoperative day in the morning, on ICU* once daily (morning)
 
 
 
▪ Renal function 
 
○ diuresis/urinary output during surgery (cumulative every 60 minutes), 1st postoperative day in the morning, on ICU* (urine 24 hour collection period is from morning until next morning about 6 o'clock)
 
○ Serum: creatinine, BUN (calculated from serum urea which will be measured)
Urine: α1-Mikroglobulin, β-NAG, creatinine measurements: baseline, on ICU* once daily, serum creatinine also on peripheral ward on post-operative days 3 and 7
 
○ Serum: HbA1c baseline
 
 
 
▪ Haemostasis 
 
○ PT, aPTT, Fibrinogen,
 
○ vWF-Ag, vWF-Ristocetin-Cofactor (vWF-RiCo),
 
○ FVIII:c,
 
○ CT, CFT, MCF ExTEM and FibTEM
measurements: baseline, intraoperatively 1h after start (ROTEM only), at the end of surgery, 1st operative day in the morning (PT, aPTT, vWF-AG, vWF-RiCo, ROTEM)
 
 
 
▪ Circulating blood volume (mLs): Calculation of according to the following formulas: 
 
○ males: <math>((0.3669 \times \text{height (m)} + 0.03219 \times \text{weight (kg)} + 0.6041) \times 1000</math>
 
○ females: <math>((0.3061 \times \text{height (m)} + 0.03308 \times \text{weight (kg)} + 0.1833) \times 1000</math>
(Nadler S, Surgery 1962, Mercuriali F, Curr Med Res Opin 1996).
baseline, 1st postoperative day (if feasible)
 
 
 
▪ Requirements of blood products (EC, FFP, PC, plasma derived coagulation factor concentrates) during surgery, intraoperative blood loss (suction volume minus rinsing fluids only)
 
▪ PONV (postoperative nausea and vomiting) on ICU* and until post-op day 5
 
▪ Adverse Events – from start of administration of Investigational product continuously until postoperative day 5 (serious adverse events which are not yet resolved on POD 5 will be followed until study end).
 
 |

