|  | 
fasting time, type of bowel preparation)
 
 
Pre-op transfusion will be administered according to standard procedure (hct. between 25 and 30%)
 
 
day 0/ prior anaesthesia:
 
 
start basal infusion of crystalloid fluid replacement: 4 ml/kg/h
 
insert thoracic epidural catheter
 
induction anaesthesia
 
 
day 0/ after induction of anaesthesia/prior surgery :
 
 
set arterial line and central venous catheter
 
set of urethral catheter and measurement of intraabdominal pressure
 
final positioning of patient in operating theatre
Note: Loading of epidural analgesia starts at the end of surgery when all study related intraoperative measurements have been performed
 
placement of oesophageal probe, calibration of PiCCO
 
baseline recording of haemodynamics (SAP, DAP, MAP, HR, CVP; oesophageal Doppler and PiCCO: CI, SV, SVR; PiCCO: ITBVI, EVLWI)
 
Blood sampling and urine sample for laboratory evaluation*
 
Concomitant medication and therapy (including concomitant medication prior induction of anaesthesia)
 
 
*Baseline laboratory
 
 
arterial blood gas analysis (pCO2, pO2, HCO3, SaO2) including acid base status (pH, BE, lactate, bicarbonate) and electrolytes (Na, K, Ca, Cl). Blood sampling for BGA should be performed as close as possible to the time, at which the corresponding hemodynamic measurement is done.
 
renal function parameters (urine: <math>\alpha</math>1-MG, <math>\beta</math>-NaG, creatinine, serum: creatinine, BUN, HbA1c)
 
haemostasis and coagulation parameter (PT, aPTT, Fibrinogen, vWF-Ag, vWF-RiCo, F VIII:c; CT, CFT, MCF using ExTEM und FibTEM)
 
Inflammatory parameters (IL6 (facultative), IL 10 (facultative), PCT, CRP, white blood cell count (WBC))
 
cardiac function parameters (Troponin or high-sensitivity Troponin, NT-Pro-BNP)
 
 
day 0/ after baseline recordings:
 
 
first bolus (250 ml/5 min) of Investigational Products
 
start of volume replacement algorithm according to oesophageal Doppler measurements
 
thereafter: start of surgery/skin incision
 
 
day 0/ during surgery (after start of skin incision):
 
 
Haemodynamics 
 
measurements following dosing algorithm (i.e. in 15 min intervals when no volume optimisation, or 15 minutes after new optimised stroke volume):
 
 
 
 |

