## **14 VISIT SCHEDULE**

### **14.1 Procedures at Each Visit**

**day -1** (range -5)/ pre-operatively:

- Verification of inclusion and exclusion criteria\*, including informed consent
- History, demographics, body weight
- Randomization
- HRQoL (EQ-5D questionnaire)
- Pre-operative medication / therapy as medically indicated and standardized (including pre-operative fasting time, type of bowel preparation)
  - Pre-op transfusion will be administered according to standard procedure (hct. between 25 and 30%)

\* blood samples for laboratory evaluation of haematocrit, renal function/serum creatinine, hepatic function/Quick value, Child-Pugh, electrolyte status/ Na, K, Ca

\* urine sample in women: for pregnancy testing

**day 0**/ prior anaesthesia:

- Start basal infusion of crystalloid fluid replacement: 4 ml/kg/h
- Insert thoracic epidural catheter
- Induction anaesthesia
- Adverse events

**day 0/** after induction of anaesthesia/prior surgery :

- Set arterial line and central venous catheter
- After set of urethral catheter measurement of intraabdominal pressure
- Final positioning of patient in operating theatre
- Placement of oesophageal probe, calibration of PiCCO
- Baseline recording of haemodynamics (SAP, DAP, MAP, HR, CVP; oesophageal Doppler and PiCCO: CI, SV, SVR; PiCCO: ITBVI, EVLWI)
- Body temperature
- Blood sampling and urine sample for laboratory evaluation\*
- Concomitant medication and therapy (including concomitant medication prior induction of anaesthesia; including blood products acc. to trigger)  
Note: Loading dose of epidural analgesia will be applied at the end of surgery after all intraoperative study related measurements have been finalized
- Adverse events

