## Baseline laboratory

- arterial blood gas analysis (pCO2, pO2, HCO3, SaO2) including acid base status (pH, BE, lactate, bicarbonate) and electrolytes (Na, K, Ca, Cl). Blood sampling for BGA should be performed as close as possible to the time, at which the corresponding hemodynamic measurement is done.
- renal function parameters (*urine*: creatinine,  $\alpha$ 1-MG,  $\beta$ -NAG; *serum*: creatinine, BUN, HbA1c)
- haemostasis and coagulation parameter (PT, aPTT, Fibrinogen, vWF-Ag, vWF-RiCo, F VIII:c; CT, CFT, MCF using ExTEM und FibTEM)
- Inflammamatory parameters (IL6 (facultative), IL 10 (facultative), PCT, CRP, white blood cell count (WBC))
- cardiac function parameters (Troponin or high-sensitivity Troponin, NT-Pro-BNP)

**day 0/** after baseline recordings:

- First bolus (250 mLs/5 min) of Investigational Products
- Start of volume replacement algorithm according to oesophageal Doppler measurements
- Thereafter: start of surgery/skin incision
- Adverse events and adverse reactions

**day 0/** during surgery (after start of skin incision):

- Haemodynamics
  - every 15 min within dosing algorithm cycle when there is no volume optimisation, or 15 minutes after stroke volume optimisation: SAP, DAP, MAP, HR, CVP; PiCCO and oesophageal Doppler: CI, SV, SVR
  - every 60 min after start of surgery: ITBVI, EVLWI (PiCCO)
- Infusion of the Investigational Products according to algorithm
- Hourly blood sampling for intraoperative laboratory evaluation\*
- Diuresis/urinary output (cumulative every 60 min)
- Concomitant medication and therapy (including inotropic drugs, sodium bicarbonate, infusion of blood products (RBC, FFP, platelets) according to the triggers
- Adverse events and adverse reactions

\*laboratory measurements in blood/serum samples:

- 1 hour after start of surgery: haemostasis/ coagulation (ROTEM only), arterial blood gas analysis (pCO2, pO2, HCO3, SaO2) including acid base status (pH, BE, lactate, bicarbonate) and electrolytes (Na, K, Ca, Cl)
- at 2 hours after start of surgery and then every 60 min intraoperatively: arterial blood gas analysis (pCO2, pO2, HCO3, SaO2) including acid base status (pH, BE, lactate, bicarbonate) and electrolytes (Na, K, Ca, Cl)

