| Blood products administration                                    | X
if requ.                                         |                                                       | X
acc.
trigger                                                                   | X
acc.
trigg    | X
acc.
trigg          |                               |                                                 |                                                  |                              |                                      |
| Blood losses                                                     |                                                       |                                                       |                                                                                        | X                     | X                           |                               |                                                 |                                                  |                              |                                      |
| Adverse events and adverse reactions                             |                                                       | X                                                     | X                                                                                      | X                     | X                           | X                             | X                                               | X                                                | X                            | X                                    |
| PONV                                                             |                                                       |                                                       |                                                                                        |                       |                             | X                             | X                                               | X                                                |                              |                                      |

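### The protocol gives two conflicting start points for adverse-event recording, and a date of onset alone cannot separate day-0 events before the first study bolus from those after it

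*Protocol*

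**What the plan says.** Two places start recording with the study product. Section 12.2, under its last group of safety variables, states: "Adverse events will be documented with start of administration of Investigational product throughout surgery". The synopsis list of secondary safety variables gives the window as "from start of administration of Investigational product continuously until postoperative day 5".

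Two places start earlier. Section 14.1 lists "Adverse events" at the day-0 step before anaesthesia, which covers the start of basal crystalloid, epidural insertion and induction. It lists the item again at the step after induction, which covers line placement and baseline measurements. In the section 14.2 table, the row "Adverse events and adverse reactions" has its first mark in the prior-anaesthesia column and its next in the pre-surgery column.

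The synopsis visit list differs again. Its step containing the "first bolus (250 ml/5 min) of Investigational Products" has no adverse-event item. The first such item comes under "day 0/ during surgery (after start of skin incision" (bracket closed in the original). The matching step in section 14.1, which begins "First bolus (250 mLs/5 min) of Investigational Products", does carry an item for adverse events and adverse reactions.

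Section 13.2.1 lists what each adverse-event description must contain. For timing it asks for the dates of onset and resolution, not a clock time.

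**The concern.** The start of the recording window decides which events exist in the database. A site that follows section 12.2 has no reason to record a hypotensive episode at induction. A site that follows section 14.1 or the table has every reason to do so. Section 8 plans three centres, and section 13.2.1 says that it wants adverse-event reporting harmonised across them, so a difference in the window works against the protocol's own aim.

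The analysis cannot fully repair this afterwards. An analysis plan can define which events count as arising on treatment, but it cannot recover events that a site did not collect. Nor can it separate pre-bolus from post-bolus events on day 0 if only the date was recorded. Events caused by anaesthesia could then be counted in each arm's rate beside events that followed the study fluid.

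**Working it through.** No figure in the protocol is at stake. The check is a comparison of the passages that bear on the start of recording.

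**When treatment starts.** Section 10.2.3 places the start of Investigational Product treatment after reliable Doppler baseline readings and before incision, with the first 250 ml bolus. Recording from the start of administration therefore means recording from that bolus.

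**The passages side by side**

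| Place | Before anaesthesia | After induction | First bolus | After incision |
|---|---|---|---|---|
| Synopsis, safety variables | no | no | yes | yes |
| Section 12.2 | no | no | yes | yes |
| Section 14.1 | yes | yes | yes | yes |
| Section 14.2 table | yes | yes (pre-surgery column) | same pre-surgery column | yes |
| Synopsis, visit list | no item | no item | no item | yes |

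Rows 1 and 2 conflict with rows 3 and 4. In the section 14.2 table, the pre-surgery column also holds the first product administration, so its single adverse-event mark spans both sides of the bolus. Row 5 states no start; it only lacks an item.

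**Whether another section settles it**
- Section 13.2.1 covers events during or following product administration and also during the course of the study. Section 15.1 starts the study at randomisation, on day -1 (range -5), so this wording supports either reading.
- Section 13.1.1 defines an adverse event by temporal association with use of an Investigational Product. That argues against counting pre-bolus events, yet sections 14.1 and 14.2 schedule their collection.

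Neither section resolves the conflict.

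**How mixing would act.** Let p be the proportion of patients with an event after the bolus. Let q be the proportion with a counted event before it, equal in both arms and independent of p. The observed proportion is 1 − (1 − p)(1 − q), so the observed difference is (1 − q) times the true one.

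The documents give neither p nor q. Assume, purely for illustration, p of 20% in one arm and 10% in the other:

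| q (assumed) | Observed rates | Difference (points) | Risk ratio |
|---|---|---|---|
| 0% | 20.0% vs 10.0% | 10.0 | 2.00 |
| 1% | 20.8% vs 10.9% | 9.9 | 1.91 |
| 2% | 21.6% vs 11.8% | 9.8 | 1.83 |
| 5% | 24.0% vs 14.5% | 9.5 | 1.66 |
| 10% | 28.0% vs 19.0% | 9.0 | 1.47 |
| 20% | 36.0% vs 28.0% | 8.0 | 1.29 |

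For q = 5%: 1 − 0.80 × 0.95 = 0.240 and 1 − 0.90 × 0.95 = 0.145, so the ratio is 0.240/0.145 = 1.66. The table shows the form of the effect, which is a pull towards no difference. It does not estimate the effect in this trial.

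**The case against.** The strongest reply is that this is a wording mismatch with little consequence.

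- **Balance.** Pre-bolus events arise after randomisation, before any blinded add-on fluid, and under the same basal infusion in every arm. They favour no arm. This stands. It rules out directional bias but not dilution or uneven collection between sites.
- **Analysis plan.** No passage says that pre-bolus events will be counted in the arm rates, and a plan that is not shown may exclude them. This stands as a limit: mixing is possible, not certain. The plan would still need an onset time or a before/after marker, which the protocol does not require. The case report form is also not shown and may have such a field.
- **Existing separation.** Section 14.1 names only adverse events at the two pre-bolus steps and adds adverse reactions from the bolus on, and each event receives a causality judgement. Events at induction would therefore not automatically be attributed to the study fluid. This stands, but it does not fix which events are collected.
- **Size.** Section 13.2.1 removes listed expected perioperative events from adverse-event reporting, so the larger values of q above may be unrealistic. This stands.

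A reader might infer a third rule, that recording starts only after incision, so that reactions to the first bolus go unrecorded. The documents do not support that. It would rest only on an item missing from the synopsis visit list. The synopsis safety list, section 12.2, section 13.2.1, the first-bolus step of section 14.1 and the pre-surgery column of the table all cover the first bolus.

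A reader might also call the prior-anaesthesia step free of any trial fluid. Basal Sterofundin ISO, the same product as the control, starts there. However, it is open-label, classed as necessary concomitant medication in section 11, and given in every arm. It is not the randomised treatment.

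**Conclusion.** The contradiction is in the current text: sections 14.1 and 14.2 start adverse-event recording before anaesthesia, while section 12.2 and the synopsis safety list start it with the study product. Because only an onset date is required, the data that the protocol asks for cannot separate the two periods on day 0.

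The consequence is modest. Sites may collect different windows, and if pre-bolus events are counted by arm, the contrast is diluted without direction. That depends on sites following section 14.1 or 14.2 and on the analysis not separating events by onset. A definite loss of power or a definite shift in risk ratio cannot be claimed, since the protocol gives no adverse-event rates and sets no power target for them. Section 16.2 treats tests of secondary variables as exploratory. Neither primary endpoint is touched.

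**What to change.** - Reconcile the synopsis safety list, the synopsis visit list, section 12.2, section 14.1 and the section 14.2 table to one stated start of adverse-event recording.
- For day-0 events, record the time of onset, or at least whether onset was before or after the start of the first study bolus, and add this to the required items in section 13.2.1.
- State that events with onset before the first bolus are reported separately and kept out of the between-arm comparison.
- Add the adverse-event item to the first-bolus step of the synopsis visit list, as section 14.1 already has it.

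The cost is protocol wording and one field on the adverse-event page. No new assessment is needed.

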## 4 INTRODUCTION

The aim of volume replacement is to compensate a reduction in the intravascular volume e. g. during surgery and to counteract hypovolaemia in order to maintain haemodynamics and vital functions. Boldt (Boldt, 2005) concluded that volume replacement should not only tend to optimize macrocirculation and oxygen delivery but also to improve organ perfusion, microcirculation and inflammatory response.

Hydroxyethyl starch (HES) is the most intensively studied artificial colloidal plasma volume substitute (Boldt & Suttner, 2005). It consists of hydroxyethylated polymers of glucose, derived from amylopectin. The characteristics of HES can mainly be defined by the molecular weight and the molar substitution ratio, i.e. the ratio of replacement of glucose group by hydroxyethyl group during production. Various HES preparations exist showing different physico-chemical properties ((Jungheinrich & Neff, 2005),(Boldt & Suttner, 2005)). The Investigational Products Tetraspan® contain HES with an average molecular weight of 130,000 Daltons, a molar substitution of 0.42 and a substitution ratio of 6:1 is solved in a balanced electrolyte solution. The cation pattern in the crystalloid component Tetraspan® is adapted to physiological plasma electrolyte concentrations. The anion pattern is a combination of chloride, acetate and malate. The purpose is to minimize the risk of hyperchloraemia and acidosis. The additions of acetate and malate instead of lactate anions are intended to reduce the risk of lactic acidosis. In conclusion, Tetraspan® combines benefits of the modern 3. generation HES 130/0.42 with proven advantages of a balanced plasma adapted electrolyte solution.

While Tetraspan® 6% (containing 6% HES) is iso-oncotic, i.e. the increase in the intravascular plasma volume is equivalent (i. e. 100%) to the infused volume, the Investigational Test Product Tetraspan® 10% (containing 10% HES) is hyper-oncotic, i. e. the volume effect is 145%. Thus, a considerable intravascular effect could be achieved without overloading the interstitial compartment with fluid and consequently reducing oedema tendency with its known pathophysiological consequences ((Lobo *et al*, 2006), (Brandstrup, 2006)).

All products used in the present phase IV trial are registered in Germany as well as in various countries in Europe. The clinical use of the Investigational Products in the present study is within the approved Summary of Product Characteristics (SmPC).

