## \* laboratory measurements in blood/serum sample:

- arterial blood gas analysis/acid base status/electrolytes. Blood sampling for BGA should be performed as close as possible to the time, at which the corresponding hemodynamic measurement is done.
- haemostasis/coagulation parameters (PT, aPTT, Fibrinogen, FVIII:c, vWF-Ag, vWF-RiCo; CT, CFT, MCF using ExTEM und FibTEM)
- cardiac function (Troponin or high-sensitivity Troponin, NT-Pro-BNP)
- inflammatory reaction parameters (facultative: IL-6, IL-10)

**day 0/** intensive care unit (ICU) –

- Aldrete Score (*on admission*)
- Haemodynamics (SAP, DAP, MAP, HR, CVP (on admission and 6hourly); PiCCO: CI, SV, SVR, ITBVI, EVLWI) (on admission and after 6 hours)
- blood gas analysis (arterial or venous blood sample) including acid base status and electrolytes: (on admission, 6 hours after admission). Blood sampling for BGA should be performed as close as possible to the time, at which the corresponding hemodynamic measurement is done.
- abdominal pressure (*6 hours after admission*)
- Ventilatory support as requested to maintain normocapnia and oxygen saturation (PCV, CPAP)
- Concomitant medication, infusion therapy (separate for colloids (i. e. gelatine) crystalloids, blood products)
- Diuresis (sampling period until next morning about 6 o'clock)
- Adverse events and adverse reactions

- check of discharge criteria

**day +1** (1st post-operative day)/ On ICU: Postoperative care will follow a standardised regimen.

- Haemodynamics (SAP, DAP, MAP, HR, CVP(every 6 hours)); PiCCO: CI, SV, SVR, ITBVI, EVLWI (every 12 hours/ in the morning and in the evening)
- abdominal pressure (in the morning)
- Ventilatory support (PCV, CPAP) as requested to maintain normocapnia and oxygen saturation
- Blood sampling for laboratory evaluation\*, urine sample for laboratory evaluation\*\*
- Aldrete Score (in the morning)
- SIRS-criteria
- Nursing Delirium Screening Scale (NuDesc) (three times daily)
- Injury scores (APACHE II, SAPS II, SOFA)
- Assessment of “fit for discharge” criteria (once on ICU - preferably in the morning)
- Concomitant medication including parenteral nutrition, infusion therapy (separate for colloids i. e. gelatine and crystalloid, blood products)
- Diuresis (Sampling period is from morning until next morning about 6 o'clock)
- PONV
- body weight (if possible)

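### The postoperative day 1 value of circulating blood volume is rescaled body weight and cannot tell intravascular from interstitial fluid

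*Protocol*

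**What the plan says.** Protocol section 12.2 (Secondary Variables - Safety, under Other) introduces the variable with "Circulating blood volume (mLs): Calculation will use the following formulas". The synopsis in section 3 does the same: "Circulating blood volume (mLs): Calculation of according to the following formulas". There is one formula for men and one for women, each a height term plus a weight term plus a constant, multiplied by 1000. The weight term and constant are "0.03219 \times \text{weight (kg)} + 0.6041" for men and "0.03308 \times \text{weight (kg)} + 0.1833" for women.

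Two time points are listed: baseline and the "1st postoperative day (if weight measurement can be performed". The schedule in section 14.1 accordingly collects "body weight (if possible" on day +1. Haematocrit, blood loss, fluid balance and haemodynamic measurements do not enter the formula.

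The introduction (section 4) says of the hyper-oncotic product that "a considerable intravascular effect could be achieved without overloading the interstitial compartment with fluid and consequently reducing oedema tendency". The study rationale (section 5) makes the same argument against iso-oncotic colloid and crystalloid alone.

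**The concern.** A formula based on sex, height and weight gives a blood volume expected for a given body size. Used once, before fluid is given, it is a reasonable descriptor. Used again the day after major surgery, its only new information is that the patient's weight has changed, and it books a fixed fraction of that change as blood.

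The trial is about where the fluid goes. A safety variable reported in mL of circulating blood volume will be read as volume status, yet it responds identically to a litre in the vessels and a litre in the tissues. A reader of the safety tables could take a larger day 1 value as a better-filled circulation when it shows only that the patient is heavier.

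**Working it through.** The protocol reports no numerical result for this variable, so there is no figure to reproduce. The check evaluates the printed formulas.

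**Inputs from the protocol (sections 3 and 12.2).** Weight coefficient: 0.03219 for men, 0.03308 for women, with the sum multiplied by 1000.

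**Change within a patient.** Sex, height and the constant cancel:

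- Men: volume on day 1 minus volume at baseline = 0.03219 × 1000 × weight change = 32.19 mL per kg.
- Women: 0.03308 × 1000 × weight change = 33.08 mL per kg.

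**Scored change over a range of weight changes.** The protocol gives no weight-change figures, so these are assumptions.

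| Weight change | Men (mL) | Women (mL) |
|---|---|---|
| -1 kg | -32 | -33 |
| 0 kg | 0 | 0 |
| +1 kg | +32 | +33 |
| +3 kg | +97 | +99 |
| +5 kg | +161 | +165 |
| +8 kg | +258 | +265 |

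**Scored change against an assumed true change.** The fluid splits are invented for illustration, and 1 L retained is taken as 1 kg.

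| Case | True blood volume change | Interstitial gain | Weight change | Scored, men | Scored, women |
|---|---|---|---|---|---|
| A | +300 mL | 1 L | 1.3 kg | +42 mL | +43 mL |
| B | 0 | 4 L | 4.0 kg | +129 mL | +132 mL |
| C | -500 mL | 5 L | 4.5 kg | +145 mL | +149 mL |

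Case B, with no true change, scores about three times case A (4.0 / 1.3 = 3.1), where blood volume really rose. Case C has the wrong sign. A full litre kept entirely in the vessels would score only 32 or 33 mL, about 3% of the truth.

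**Scale.** For an assumed man of 75 kg and 1.75 m the formula gives (0.3669 × 1.75 + 0.03219 × 75 + 0.6041) × 1000 = 3660 mL, so +161 mL is 4.4%. For an assumed woman of 65 kg and 1.65 m it gives (0.3061 × 1.65 + 0.03308 × 65 + 0.1833) × 1000 = 2839 mL, so +165 mL is 5.8%.

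**The case against.** The strongest reply is that little harm follows. The variable is secondary, and section 16.2 treats all secondary tests as exploratory. The scored effect is about 32 to 33 mL per kg. Section 12.2 already plans intrathoracic blood volume index and extravascular lung water index by PiCCO at baseline, during and at the end of surgery, on ICU admission, 6 hours later and 12-hourly on ICU from day 1. A careful reader would use those. All of this stands, and it limits the weight of the point.

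A reader might infer something stronger: that the variable would turn the comparison between arms round, showing the opposite of what the trial hopes to find. The protocol does not support that. It gives no expected weight changes and states no direction for this variable. Sections 4 and 5 describe how the product should work but do not name this calculation as the test of it. With equal weight gain in all arms, the scored changes would be nearly equal, not turned round. Nor does the formula count oedema alone: true plasma expansion also adds weight and is scored at the same rate.

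It can also be said that reporting weight change in kg carries the same information, with the same gaps where patients could not be weighed. That is correct. What is gained is a label that does not claim to be blood volume.

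**Conclusion.** The point holds, in limited form. As defined, the day 1 value adds only a sex-specific multiple of weight change to the baseline value and cannot distinguish fluid in the circulation from fluid in the tissues. This follows from the printed formulas and needs no assumption.

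What it would do to the comparison between arms is conditional. If the comparator arms gain more interstitial fluid and hence more weight, as sections 4 and 5 lead one to expect, they could be credited with a larger rise in circulating blood volume, by about 32 to 33 mL for each kg of difference in mean weight gain. That size rests on weight differences the protocol does not state. A reversed result is a possibility under that premise, not something the document shows.

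The baseline calculation can remain as a body-size descriptor. The primary endpoints, alpha and sample size are unaffected.

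**What to change.** - In the synopsis (section 3) and section 12.2, keep the formula at baseline only, described as a body-size estimate, and delete the postoperative day 1 calculation.
- Report body-weight change from baseline to day 1 in kg, with the number of patients weighed in each arm, since weighing is done only where possible.
- For volume status and lung water on day 1, refer to the intrathoracic blood volume index and extravascular lung water index already measured by PiCCO on ICU.

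The cost is wording in two places. No new data are needed, and nothing is lost, because the deleted value can be rebuilt from weight.
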